The target population was (a) any patient who has received a blood transfusion for any reason at four hospitals, (b) any patient who had G&S blood samples taken for compatibility testing for any clinical reason during the evaluation period, (c) all clinical staff involved in taking G&S blood samples or administering blood units to patients at four hospitals, and (d) supervisors who delivered the BETC training sessions to clinicians.

### 
Outcome measures

2.6

A summary of outcome measures, definitions, and data sources are reported in Table 1. Benefits to patients will be measured by the reduction in transfusion‐related errors, as proxied by the following five outcomes:Number and rate of mislabelled samples*.Number and rate of wrong blood in a tube*.Number and rate of patients who receive wrong blood due to errors related to bedside checks**.Number and rate of patients who are misidentified at the point of transfusion**.Number and rate of wrong blood units collected from the fridge due to errors related to bedside checks.

**TABLE 1 tme70002-tbl-0001:** Outcome measures for the evaluation of BETC implementation.

Outcome measures	Definitions	Data sources
Measures for benefits to patients		
Mislabelled samples	Samples contain incorrect information of the patient	Winpath, BloodTrack Manager
Wrong blood in a tube	A G&S sample contains blood from the wrong patient	Winpath, BloodTrack Manager, national hemovigilance scheme
Patients received wrong blood due to errors related to bedside checks	Administration of an incorrect blood unit to a patient due to failure in verifying patient identity and blood group compatibility	DATIX and national hemovigilance scheme
Patients are misidentified at the point of transfusion	A patient is incorrectly identified before receiving a blood transfusion	DATIX and national hemovigilance scheme
Wrong blood units collected from the fridge due to errors related to bedside checks	Incorrect blood units from storage due to failures in verifying patient details and blood group compatibility	DATIX and national hemovigilance scheme
Measures for clinician time saved		
Mislabelled samples	Time spent on G&S sample collection, labelling, analysis and reporting.	Process mapping
Wrong blood in a tube	Time spent on G&S sample collection, labelling, analysis, reporting.	Process mapping
Manually labelling blood samples	Time spent on writing patients' details for G&S labelling	Process mapping

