Manually writing post‐administration documents	Time spent on recording transfusion details after blood administration	Process mapping
Having second nurse for blood administration	Time spent by second nurse for compatibility check	Process mapping
Completing traceability documentations	Time spent on documenting and tracking blood transfusion details	Health Economics Inventory
Spillover effect	Time saved from a whole blood transfusion process after implementing the BETC	Process mapping
Measures for savings from material and consumable use		
Mislabelled samples	Material and consumable costs for G&S sample collection and labelling	Health Economics Inventory
Wrong blood in a tube	Material and consumable costs for G&S sample collection and labelling	Health Economics Inventory

**In cases where outcomes 1 and 2 overlap, the events will be counted only once, under outcome 2*.

***Errors that occurred at the point of transfusion, will be counted as outcome 4. Other errors will be counted as outcome 3, that is, ‘errors related to bedside checks’*.

Two types of hospital cost savings, as the results of the BETC implementation, will be assessed.Clinician time saved: Time saving will be generated from six sources including time spent on (1) re‐sampling because of mislabelled samples, (2) re‐sampling because of wrong blood in a tube, (3) manually writing blood sample labels, (4) manually writing post‐administration documents, (5) having a second nurse for blood administration, and (6) completing traceability documentations. Also, the implementation of BECT on steps 1, 9, and 10 might generate a spillover effect to other steps, and as a result save clinician time further.Reduction in material and consumable use: Savings will be generated from re‐sampling because of (1) mislabelled samples and (2) having wrong blood in a tube.

### 
Data collection

2.7

Data will be collected from three sources: (1) transfusion datasets: electronic laboratory databases Winpath and BloodTrack Manager, hospital‐based incident reporting schemes (or DATIX), and reports submitted to the national hemovigilance scheme, (2) Process mapping dataset, and (3) Health Economics Inventory dataset. The process mapping and Health Economics Inventory datasets were developed specifically for this evaluation study.

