#### Process mapping dataset

2.7.2

The process mapping dataset provides information about the time spent by clinicians in each step of the transfusion process. A structured data collection approach was used to map the transfusion process across the four hospitals within Barts Health NHS Trust. Clinician‐level time spent data were collected using a standardised audit form, a time‐in‐motion method, and a stopwatch to record process durations systematically. A data collection form was developed to capture the clinician time spent in hospital wards and staff time spent in the laboratories for blood transfusion.

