#### Cost savings within the evaluation period

2.8.2

Cost savings will be quantified by the monetary value of reduction in (1) clinician time used for completing transfusion‐related tasks and (2) transfusion‐related material and consumable use. We identified seven sources of savings for clinician time and two sources of savings for material and consumable use, as reported in Table 1.

For six (out of seven) sources of clinician time saving associated with BETC implementation, we will estimate the amount of time saved from each source by combining the time saved from one transfusion to the number of relevant transfusions. These will then be converted to monetary value by applying the hourly rate of clinicians.^21^, ^22^ Costs will be presented at 2023/24 level. For traceability, the monetary value of clinician time saved will be estimated by the proportion of salaries for two Transfusion Practitioners in Barts Health NHS Trust for their time spent on supporting the traceability of transfusions under the manual transfusion system. Regarding the two sources of cost savings in material and consumable use, for each source, we will identify and then quantify the material and consumable use items saved from one transfusion, followed by converting the quantities to monetary value by applying the unit cost for each item, and finally to estimate cost savings by combining monetary value from one transfusion to the number of relevant transfusions.

During the 2‐year implementation period, the PDA uptake did not reach 100% for many wards. Therefore, we will report two types of annual cost savings, that is, actual savings and potential savings when the maximum PDA uptake is achieved.

#### 
BECT implementation and staff training costs

2.8.3

We will report the actual implementation costs occurred at the Trust and year level. The costs include salary for implementation staff, costs for software licences, PDA hardware maintaining and software support fee, costs for PDA devices and mobile printers. Training costs for clinicians to learn how to use the PDA device will be calculated at clinician level by applying clinicians' hourly rate to the time spent on training sessions.

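### Table 1 defines the spillover saving over the whole transfusion process while section 2.6 confines it to other steps; if the Table 1 version is costed and summed, itemised time savings enter twice.

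*Protocol article*

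**What the plan says.** Three places in the protocol article bear on this.

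- **Section 2.6, text on cost savings.** "Time saving will be generated from six sources including time spent on" the six listed activities: re-sampling for mislabelled samples, re-sampling for wrong blood in a tube, writing labels by hand, writing post-administration documents, the second nurse, and traceability paperwork. It then adds that BETC at steps 1, 9 and 10 "might generate a spillover effect to other steps, and as a result save clinician time further".
- **Table 1, clinician-time block.** Seven rows: the six activities and spillover. The spillover row is defined as "Time saved from a whole blood transfusion process after implementing the BETC", with process mapping as its source. Among the other rows are "Manually labelling blood samples" and the second-nurse row, defined as "Time spent by second nurse for compatibility check"; both also come from process mapping.
- **Section 2.8.2.** "We identified seven sources of savings for clinician time and two sources of savings for material and consumable use", with a reference to Table 1. For six of the seven clinician-time sources, "we will estimate the amount of time saved from each source by combining the time saved from one transfusion to the number of relevant transfusions", and the result is priced at clinicians' hourly pay. The one exception is traceability, valued from part of two Transfusion Practitioners' salaries. Spillover is therefore one of the six. Annual savings are to be reported both as realised and as projected at maximum device uptake.

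**The concern.** The two descriptions of spillover are different quantities. Section 2.6 describes a remainder: what is saved elsewhere in the pathway, on top of the itemised activities. Table 1 describes a total: what is saved across the pathway, itemised activities included. The caption of Figure 1 names steps 1, 9 and 10 as those BETC replaces, so they belong to the process that Table 1 refers to.

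This matters because section 2.8.2 takes its list of sources from Table 1, so the table's wording is the one an analyst would most naturally follow when costing. A total placed beside its own components, and added to them, counts those components twice. Any such error would carry into both the realised and the maximum-uptake savings, which are meant to inform decisions on wider NHS roll-out.

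Overlap is dealt with elsewhere: the notes to Table 1 set once-only rules for overlapping error outcomes. No equivalent rule covers the time-saved rows.

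**Working it through.** The plan states no savings figure, so there is none to reproduce. The check is an accounting identity.

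**Which source is the seventh?** Section 2.6 lists six clinician-time sources and section 2.8.2 counts seven. The only clinician-time row in Table 1 that is not among the six is spillover. It is therefore costed as a source of its own, by the same time-per-transfusion method as the other process-mapped rows.

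**Which rows overlap with a whole-process measure?**

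| Table 1 row | Inside whole-process time? |
|---|---|
| Manual labelling | Yes, step 1 |
| Second nurse | Yes, step 9 |
| Post-administration documents | Yes, taking them as part of step 9 or 10 (the text assigns no number) |
| Traceability | Any step 10 time that is mapped; valued separately through salaries |
| Re-sampling, mislabelled samples | Not necessarily; arises from avoided repeat samples |
| Re-sampling, wrong blood in a tube | Not necessarily; same reason |

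**Notation**, all on the same count of transfusions:
- D = direct saving in the overlapping itemised rows
- O = saving in steps other than 1, 9 and 10
- W = D + O = whole-process saving

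**Totals for these components if the sources are summed**
- Section 2.6 definition: D + O = W
- Table 1 definition: D + W = 2D + O

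The excess is D. As a ratio it is (2D + O)/(D + O) = 2 − f, where f = O/W.

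**Size.** The documents do not give f or O/D, so the values below are assumed.

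| Share of W from other steps, f | Overstatement factor 2 − f |
|---|---|
| 0 | 2.00 |
| 0.25 | 1.75 |
| 0.50 | 1.50 |
| 0.75 | 1.25 |
| 1 | 1.00 |

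In terms of O/D, O = 0.5D gives 2.5/1.5 = 1.67. If the other steps become slower, O is negative and the factor exceeds 2: O = −0.2D gives 1.8/0.8 = 2.25.

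**Dilution by re-sampling.** Let R be the re-sampling time saving, which need not overlap. The factor for the process-mapped total is then (R + 2D + O)/(R + D + O). For O ≥ 0 this is below 2 whenever R is above zero.

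**Can the remainder be computed?** Section 2.7.2 says process mapping records "the time spent by clinicians in each step of the transfusion process", so time in the other steps can be separated from time in steps 1, 9 and 10.

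**The case against.** The best defence is that the non-overlapping definition is already in the plan. Section 2.6 limits spillover to other steps and calls it a further saving, which is also the ordinary meaning of the word. It introduces Table 1 as a summary, so the fuller text could be read as governing. No formula for a grand total is printed, and how sources are combined is something a condensed article may fairly leave to a fuller document. The step-level data would let the analysts do it correctly.

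Much of this stands. A reader might infer that the plan does count these savings twice. The documents do not support that, because no summation rule is shown and section 2.6 points to the non-overlapping intent. Three further inferences also go too far:

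- That the process-mapped saving is exactly doubled. The two re-sampling rows also come from process mapping and need not overlap, and a factor of 2 on the remaining components requires O = 0.
- That clinician time is the largest savings stream. It supplies seven of the nine sources, but no amounts are given.
- That a net cost would turn into a net saving. No cost or saving figure is given, implementation and training costs are reported under a separate heading (section 2.8.3), and no net formula is stated.

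The defence does not remove the conflict itself. The Table 1 definition is stated, not omitted, and section 2.8.2 refers to that table when it lists the sources to be costed. An analyst who follows it and adds the rows gets an inflated figure, and nothing in the article would stop this.

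**Conclusion.** The point holds as an inconsistency between stated definitions that creates a risk of double counting. Table 1 and section 2.6 cannot both define the spillover measure, and section 2.8.2 costs it as a separate source with no netting rule.

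The overstatement is conditional on two things: that the Table 1 definition is the one applied, and that the seven sources are summed. The overlapping components are then overstated by D, a factor between 1 and 2 for O ≥ 0 and above 2 if the other steps slow down (with W still positive). The factor rests on a common transfusion count and on an assumed O/D. It applies only to manual labelling, post-administration documents, the second nurse and any step 10 time included in the whole-process timing. It does not apply to the savings total as a whole.

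**What to change.** Either of two corrections resolves it.

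1. Redefine the spillover row in Table 1 as the manual-minus-BETC time difference in steps other than 1, 9 and 10, allowing negative values, and state in section 2.8.2 that the seven sources are mutually exclusive.
2. Use the whole-process manual-minus-BETC difference as the process-time total and show the overlapping rows only as its breakdown. Re-sampling savings stay separate where they fall outside the timed process, and step 10 time is valued either here or through the Transfusion Practitioner salaries, not both.

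The first is closer to the existing section 2.6 text. Either takes one table row and a sentence or two, and needs no new data because process mapping is recorded by step. The downside is that the estimated saving may be smaller than under the Table 1 wording.

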## METHODS AND ANALYSES

2

The implementation adopted a non‐randomised, staggered, multi‐phase design. Regression‐based time‐series intervention analyses and descriptive analyses will be applied to evaluate the impacts of BETC implementation. Research Ethics Committee approval (REC Reference Nr 22/NW/0138) and Health Research Authority approval (Nr 311 676) were obtained.

### 
Pre‐implementation status

2.1

Barts Health NHS Trust comprises four hospitals. Between these, in 2022, ~ 65 000 blood units were administered to ~15 000 patients. The blood transfusion process begins with a clinician's decision to prescribe a transfusion and ends with the administration of the blood unit to the patient. Across the four hospitals, blood transfusion follows a standardised 10‐step procedure, as outlined in Figure 1. Of these, seven steps are currently supported by the electronic system, while step 1 (blood sample collection and labelling), step 9 (blood administration), and step 10 (traceability of the blood unit) are performed manually.

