**FIGURE 1 tme70002-fig-0001:**
[figure not shown]
Transfusion process steps under manual and BETC systems. Steps 1, 9 and 10 under the manual system will be replaced by the BETC.

PPI checks must be performed every time for steps 1 and 9. In the manual process, step 1 requires that labelling on the blood sample and the request form is handwritten, where the clinician is required to write the patient's full name, date of birth, hospital number, NHS number, date and time when the sample is taken, and provide his/her signature. For step 9, prior to blood administration, PPI must be performed by two nurses who are required to check that the patient's details on the wristband match those on the blood unit and the compatibility label that is attached to the blood unit. For step 10, clinicians must return the traceability tag attached to the blood unit from the ward to the laboratory, where an individual will enter this information in the transfusion electronic system—this confirms the fate of the unit and is called traceability.

### 
Intervention

2.2

The intervention consists of a portable handheld scanning device (or Personal Device Assistance [PDA]) and a mobile printer. For the sample labelling (step 1), the PDA obtains the patient's details electronically via scanning the patient's 2D barcode on the wristband, which is embedded with the patient's details from the patient's electronic record and, in doing so, supports PPI. The PDA then communicates via Bluetooth with the mobile printer to print the label, which is then attached to the blood sample. For blood administration (step 9), the device uses the same 2D barcode to obtain and verify the patient's details against the compatibility label attached to the blood unit. For traceability (step 10), information on the use of blood is transmitted electronically every time a unit is being transfused using the PDA. It should be noted that the BETC can only be used if patients wear wristbands; consequently, these devices will not be implemented in areas where this was not the case (e.g., the outpatient setting for group and screen [G&S] samples).

The routine clinical care of patients receiving transfusions or needing blood samples will not be altered for the purpose of this study.

### 
Theory of change

2.3

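### Spillover time is priced as a BETC saving although it is a residual change in steps BETC does not replace, and no contrast is stated that would separate it from background drift

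*Protocol article*

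**What the plan says.** Section 2.1 states that "blood transfusion follows a standardised 10‐step procedure", of which "seven steps are currently supported by the electronic system". The Figure 1 caption adds: "Steps 1, 9 and 10 under the manual system will be replaced by the BETC". Steps 2 to 8 are therefore not replaced.

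Section 2.6 lists six sources of clinician time saved and then adds that BETC "might generate a spillover effect to other steps, and as a result save clinician time further". Table 1 carries spillover as a seventh row, sourced from process mapping, but defines it differently: "Time saved from a whole blood transfusion process after implementing the BETC".

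Section 2.8.2 confirms the count: "We identified seven sources of savings for clinician time and two sources of savings for material and consumable use". It then sets the valuation rule. "For six (out of seven) sources of clinician time saving associated with BETC implementation", time is obtained by "combining the time saved from one transfusion to the number of relevant transfusions" and converted to money with hourly rates. The one exception is traceability, which is valued from salaries.

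Section 2.8.1 and the Discussion give the regression-based, multiple-baseline time series for mislabelled samples only.

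**The concern.** Writing labels, writing post-administration documents, the second nurse's check and manual traceability are tasks that BETC takes away or changes, and re-sampling is a countable event. For these six sources the link from BETC to the saving is direct. Spillover has no such task or event behind it: it is whatever difference in clinician time appears in the remaining steps. Over a 36-month evaluation those steps can become faster or slower because of staffing, laboratory workload or case mix. Without a stated counterfactual, such drift goes into the estimate in full and is multiplied by annual volume.

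The Table 1 definition adds a second difficulty. A whole-process time saving includes steps 1, 9 and 10, whose savings the six task-specific sources already value. Adding the two would count part of the saving twice.

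The results are meant to feed potential savings at maximum uptake (section 2.8.2) and decisions on wider NHS roll-out (Discussion), so a misattributed component would be carried into both.

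**Working it through.** The article states no savings figure, audit size or variability for this component, so there is no figure of its own to reproduce. The checks are a count, a scaling and an illustration.

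**1. Is spillover scaled and priced?**
- Steps not replaced: 10 − 3 = 7 (steps 2 to 8).
- Clinician-time sources: 6 named in section 2.6 + spillover = 7, matching section 2.8.2.
- Sources under the volume rule: 7 − 1 (traceability) = 6. Spillover is one of them.

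**2. What does a minute of drift become?** Hours per year = volume × minutes ÷ 60. The volume is about 65,000 units in 2022 (section 2.1); treating one unit as one transfusion is an assumption.
- 0.5 minute: 65,000 × 0.5 ÷ 60 = 542 hours.
- 1 minute: 65,000 × 1 ÷ 60 = 1,083 hours.
- 5 minutes: 65,000 × 5 ÷ 60 = 5,417 hours.

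At an assumed GBP 20 to 50 per hour, one minute is about GBP 21,700 to 54,200 a year. If the relevant steps occurred only once per patient (about 15,000 patients, section 2.1), one minute would be 15,000 ÷ 60 = 250 hours. The range is therefore about 250 to 1,083 hours per minute of drift, and lower still for actual savings while uptake is incomplete.

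**3. Drift against noise.** Assume a standard deviation of 10 minutes, 100 independent audits per group and period, no true spillover and 1 minute of background drift.
- Before-after difference: SE = 10 × √(2/100) = 1.41 minutes; 95% half-width 1.96 × 1.41 = 2.77 minutes, which scales to about 3,003 hours a year.
- Difference minus the concurrent difference at sites not yet using BETC: SE = 10 × √(4/100) = 2.00 minutes; half-width 3.92 minutes.
- Simulation of 20,000 repetitions: mean apparent saving 1.01 minutes before-after (SD 1.42), against 0.03 minutes with the concurrent contrast (SD 2.01).

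Drift passes straight into the before-after figure, and the concurrent contrast removes it at the price of more noise. Over assumed standard deviations of 5 to 20 minutes and 30 to 300 audits per period, the scaled before-after half-width runs from about 870 to 10,965 hours a year, so an interval is needed whichever contrast is used.

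**4. Is the plausible mechanism already counted?** Section 2.3 expects fewer re-bleeds and less laboratory processing. Table 1 defines the time for mislabelled samples and for wrong blood in a tube as collection, labelling, analysis and reporting. That re-sampling work is thus already valued under the first two sources. Dropping the two-sample rule, also mentioned in section 2.3, is not among the six and could be a true additional effect.

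**The case against.** The strongest reply is that this is a condensed article. It gives no dates, contrast or number of observations for the process-mapping audits, and Table 1's wording could also fit manual and BETC observations made at the same time on wards at different stages of uptake. That stands in part: the article does not rule out a concurrent comparison, and a fuller plan may contain one. What the article does fix is that spillover is counted, scaled and priced, and it confines its controlled analysis to a different outcome.

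A reader might infer more than the text supports, in three ways:
- **That steps 2 to 8 cannot change, so any spillover is spurious.** The article says only that these steps are not replaced, and section 2.3 gives a route by which work elsewhere could fall. The steps cannot be treated as a clean negative control.
- **That audit noise is booked as a saving.** Sampling error is symmetric. It widens the uncertainty but creates no saving on average unless unfavourable results are discarded.
- **That only reductions are counted.** The wording expresses a hedged expectation of savings. Nothing says that increases would be dropped or set to zero.

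It is also fair to object that the drift itself is hypothetical, and that a concurrent contrast has limits. The Haematology Day Units piloted BETC at all four hospitals, and once Hospital 4 is rolled out no hospital without BETC remains.

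**Conclusion.** The point holds as a weakness of definition and attribution. Spillover enters the clinician-time savings on the same footing as six task-specific sources, yet it is a residual difference with two conflicting definitions and no stated means of separating BETC from background change. Each minute of drift per transfusion would add about 1,083 hours a year at 65,000 units, if one unit is one transfusion and all are relevant; fewer relevant transfusions reduce this in proportion. The monetary values, audit standard deviation, audit numbers and amount of drift are all assumptions. They show sensitivity and do not estimate an actual error. The documents do not show that the estimate will be wrong, or in which direction. The change is worth making because it is cheap and also settles the conflict between section 2.6 and Table 1.

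**What to change.** In section 2.6, Table 1 and section 2.8.2:

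1. Define spillover as the change in clinician time in steps 2 to 8 only, replacing the whole-process definition in Table 1.
2. Report it separately from the sum of the six task-specific savings, with its sign (including any increase) and a confidence interval.
3. Attribute it to BETC only as the change after roll-out minus the concurrent change on wards or at hospitals not yet using BETC, where the process-mapping dates allow, leaving out the Haematology Day Units. Where the dates do not allow this, report the change descriptively without attributing it to BETC.
4. If dropping the two-sample rule is the intended route, name it and value it directly, as is done for the other sources.

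The cost is some rewording and, if suitably dated observations exist, one further contrast on process-mapping data. The contrast is noisier (SE 2.00 against 1.41 minutes under the assumptions above), and the headline saving may be smaller.

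### The consumable saving is gross: it counts materials from avoided re-samples but does not charge the printed label that BETC adds to each sample it labels

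*Protocol article*

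**What the plan says.** Section 2.6 limits the consumable outcome to two sources: "Savings will be generated from re‐sampling because of (1) mislabelled samples and (2) having wrong blood in a tube". Table 1 has the same two rows, and section 2.8.2 repeats the count: "two sources of savings for material and consumable use, as reported in Table 1". Section 2.8.2 also gives the method. For each source the team "we will identify and then quantify the material and consumable use items saved from one transfusion", applies a unit cost to each item, and scales up by the number of relevant transfusions. The same section describes the quantity being valued as a reduction in consumable use.

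On the process itself, section 2.1 says that under the manual system "step 1 requires that labelling on the blood sample and the request form is handwritten". Under BETC, section 2.2 says the handheld device "communicates via Bluetooth with the mobile printer to print the label, which is then attached to the blood sample".

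Section 2.8.3 describes the cost side: "The costs include salary for implementation staff, costs for software licences, PDA hardware maintaining and software support fee, costs for PDA devices and mobile printers". Clinician training time is costed separately there. The Health Economics Inventory (2.7.3) collects consumable costs for sample collection and labelling. Table 1 uses them only in the two savings rows.

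**The concern.** A reduction in use is a difference between two totals: what the manual process consumed and what BETC consumes. The rule in 2.6 and 2.8.2 has a term for items no longer used and none for items newly used. BETC introduces at least one new item, a printed label on each sample it labels. The cost list in 2.8.3 names the printer but not what it prints.

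The two terms also apply to different numbers of samples. The saving arises only on samples that no longer have to be repeated, whereas the label is used on every BETC-labelled sample. A cheap item used on all of them can offset a dearer item saved on a few. The estimate at maximum uptake inherits the problem, because label use rises with uptake just as avoided re-samples do. The article says its micro-costing will yield accurate costs and savings and that the results will inform wider UK roll-out, so an unbalanced consumable line would carry forward.

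**Working it through.** The article states no consumable figure, rejection rate or price, so there is nothing to reproduce. The check is a break-even calculation.

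**Inputs from the article**
- Savings counted: re-samples avoided after mislabelling or wrong blood in tube (2.6, Table 1, 2.8.2).
- Added item: one printed label per BETC-labelled sample (2.2), against handwriting (2.1).
- Cost items named: implementation staff, licences, maintenance and support, devices and printers, plus training time (2.8.3). Labels are not named.

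**Quantities the article does not give (assumptions, with ranges)**
- d, the absolute fall in the share of samples that must be repeated: 0.5% to 5%.
- r, the consumable cost of one re-sample: £0.50 to £5.
- l, the cost of one printed label: £0.01 to £0.10.
- N, the number of BETC-labelled samples.

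**Formulas**
- Saving as planned = N × d × r.
- Saving after charging labels = N × (d × r − l).
- Break-even: l = d × r.

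N multiplies both lines, so the ratio of planned to label-adjusted saving, d × r / (d × r − l), does not depend on uptake. The proportional error is the same at actual and at maximum uptake.

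**Break-even label cost**
- Lowest in the range: 0.005 × £0.50 = 0.25p.
- At d = 2%, r = £1: 0.02 × £1 = 2p.
- Highest in the range: 0.05 × £5 = 25p.

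**Illustrations per 10,000 BETC-labelled samples**

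| d | r | l | As planned | Labels | After labels |
|---|---|---|---|---|---|
| 2% | £1 | 1p | £200 | £100 | +£100 |
| 2% | £1 | 5p | £200 | £500 | −£300 |
| 3% | £2 | 10p | £600 | £1,000 | −£400 |
| 5% | £3 | 5p | £1,500 | £500 | +£1,000 |

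The result takes either sign within the assumed range.

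**A term that works the other way**

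The Background and section 2.3 say BETC may remove the need for a second group-and-screen sample. The consumables this would save are also absent from the two listed sources. Let s be second samples dropped, as a share of BETC-labelled samples, each saving r. The balance becomes N × [(d + s) × r − l]. In the second row above, s = 3% gives 10,000 × (0.05 × £1 − £0.05) = £0, so the £300 deficit disappears. Charging labels alone is therefore not a complete net figure either.

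**The case against.** The strongest reply is that savings and costs are reported in separate sections, so a gross savings line is legitimate provided added use appears on the cost side. That is right as a matter of layout, and it is why a line in 2.8.3 would be a full remedy. But the cost side as written does not name labels.

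It can then be said that the 2.8.3 list is introduced as what the costs include, so it may not be exhaustive; that label stock could fall within the actual costs incurred by the Trust; that the Inventory already collects labelling consumables; and that a condensed article may leave itemisation to a fuller document. The first two points stand as possibilities, so one cannot say that no offset will be counted anywhere. They do not settle the matter. The consumable sources are enumerated, counted and given a formula. The cost items match the system and staff costs collected by the Inventory. Labelling consumables are assigned only to the savings rows. The label price may be available, but no stated step applies it to BETC-labelled samples.

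A reader might infer that the planned saving has the wrong sign, or is overstated by some definite factor. The article does not support that. Every rate and price above is assumed, and omitting dropped second samples works in the opposite direction. Nor does every sample carry a printed label: BETC is not used where patients wear no wristband, such as outpatient group-and-screen sampling, and uptake was below 100% in many wards.

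**Conclusion.** The point holds in limited form. Followed as written, 2.6 and 2.8.2 produce a gross consumable saving under the name of a reduction in use, and the label BETC adds is neither subtracted there nor named in 2.8.3. This rests on the text alone.

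The size is undetermined. Break-even runs from 0.25p to 25p per label over the assumed ranges, so a negative balance is possible but not shown. The direction of error in a fully net figure is also not established, because consumables from dropped second samples are left out too. Consumables supply two of the nine saving sources in Table 1, and the article gives no value for their share, so the effect on total savings cannot be judged. The change is worth making because it is cheap and the omission is systematic.

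**What to change.** Count label and printer consumables once, as the number of BETC-labelled samples times the unit cost. Either subtract them in 2.8.2 or add them as a recurrent line in 2.8.3, but not both. Do this for the actual and the maximum-uptake estimates, using the matching number of labelled samples in each.

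If the consumable figure is presented as net, also credit the consumables saved from second group-and-screen samples actually dropped. If it stays gross, label it so and point to the cost line that offsets it.

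The label part needs one unit price and one count. The Inventory already covers labelling consumable costs, and BloodTrack Manager records device use, so both may come from planned sources. Crediting dropped second samples needs a count of those samples as well. The downside is that the stated saving may become less favourable.
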